### **Reporting in Medical Records**

If a study participant does not have an Emory medical record, one will be established since Emory providers or facilities are furnishing services and procedures for this trial. Copies of the consent form/HIPAA authorization will be placed in the Emory medical record. Emory may generate study information about the participants that can assist with care. For example, results of 'main' study tests or procedures (spirometry) may help with management of certain study subjects. Clinical trial results may therefore be placed in the Emory medical record. Anyone with access to the medical records will therefore also have access to all relevant study information. The confidentiality of the study information in the medical record will be protected by measures such as HIPAA, although state and federal laws may not protect the research information from disclosure.

The results of some study tests and procedures will be used only for research purposes and will *not* be placed in the medical record. For example, such items include: information resulting from the skin punch biopsy used to test *in vitro* cell response to Trikafta™. *In vitro* CFTR testing and

## **10. Study Timelines**

From screening to the last follow-up visit, individual participant's participation in the study will be approximately 4 months.

Anticipated enrollment of all study participants will require 2 years.

The estimated date for the investigators to complete this study is August 31, 2025.

## **11. Inclusion and Exclusion Criteria**

In order to gain information regarding numbers of individuals with NCFBE who may be eligible for our trial, patients at Emory followed with a diagnosis of bronchiectasis (who do not have clinical criteria sufficient for a diagnosis of cystic fibrosis) will be asked to consider participating in a 'lead in' study that will determine the subject's CFTR genotype and sweat chloride. A separate consent form will be utilized for the 'lead in' study. We anticipate approximately 300 subjects will participate in the 'lead-in' study.

Subjects who exhibit a single CF-causing mutation in CFTR (e.g., F508del) and/or sweat chloride 30-60 mEq/L will be approached about their interest in reviewing the consent form for the 'main' study ("iPSC derivation and *in vivo* Trikafta™ treatment for 4 weeks").

### **Details regarding the 'main' study**

We anticipate the screening and enrollment visit for the 'main' study will require 4-6 hours to complete the informed consent, medical history, O2 saturation, concomitant medication review, physical exam, safety laboratory assessments (CBC/Diff, RENAL/LFT chemistry panel, and urinalysis), EKG, CFTR genotyping, questionnaire, serum pregnancy test for females, sweat chloride test, and spirometry.

#### **Inclusion Criteria:**

- Provision of signed and dated informed consent form
- Stated willingness to comply with all study procedures and availability for the duration of the study
- Male or Female age ≥18
- Radiologic and other clinical evidence leading to a diagnosis of NCFBE
- 1 CF-causing mutation and/or sweat chloride measurement ≥ 30 mEq/L and ≤ 60 mEq/L
- Able to perform spirometry meeting ATS criteria for acceptability and repeatability, and FEV1 40-90 mEq/L
- Clinically stable in the past 4 weeks with no evidence of bronchiectasis exacerbation (prior to Screening AND Day 1)
- Willingness to use at least one form of acceptable birth control including abstinence or condom with spermicide. This will include birth control for at least one month prior to screening and agreement to use such a method during study participation for an additional four weeks after the last administration of Study Drug

**Protocol Title: Evaluating Trikafta for the treatment of patients with non-cystic fibrosis bronchiectasis (NCFBE)**

---

- Ability to take Trikafta™
- Agreement to adhere to all current medical therapies as designated by the study physician

**Exclusion Criteria**

- Diagnosis of cystic fibrosis
- Documented history of drug or alcohol abuse within the last year
- Pulmonary exacerbation or changes in therapy for pulmonary disease in the 4 weeks prior to screening
- Listed for lung or liver transplant at the time of screening
- Cirrhosis or elevated liver transaminases > 3X ULN
- Pregnant or breastfeeding
- Inhibitors or inducers of CYP3A4, including certain herbal medications and grapefruit/grapefruit juice, or other medicines known to negatively influence Trikafta™ administration
- History of solid organ transplant
- Active therapy for non-tuberculosis mycobacterial infection or any plan to initiate non-tuberculosis mycobacterial therapies during the study period
- Known allergy to Trikafta™
- Treatment in the last 6 months with an approved CFTR modulator
- Any other condition that in the opinion of the lead investigators might confound results of the study or pose an additional risk from administering Study Drug
- Treatment with another investigational drug or other intervention within one month prior to enrollment, throughout the duration of study participation, and for an additional four weeks following final drug administration.
- Evidence of cataract/lens opacity determined to be clinically significant by an ophthalmologist at or within 3 months prior to the Screening Visit

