### **7. Statistical Analysis Plan**

Goals of the 'main' study are to determine the clinical response to Trikafta™ and whether *in vitro* responsiveness of iPS cell-derived airway monolayers predict Trikafta™ effectiveness. Primary outcomes comprise the ability of iPSC-derived monolayers to predict respiratory benefit from Trikafta™ after 4 weeks of *in vivo* treatment. Primary analysis will include an estimate of clinical response rate of Trikafta™ at week 4 of treatment and a 95% confidence interval using the exact method proposed by Blaker (Blaker, 2000). A responder is defined as any subject with an improvement, from baseline, in  $FEV_1 > 5\%$  predicted.  $FEV_1$  will also be considered continuously. A two-sided 0.05 alpha level paired t-test comparing the baseline and week 4  $FEV_1$  measurements, along with the test and 95% associated confidence interval, will be evaluated.

In this study, if at least 15% of subjects meet the definition of responder, we will view this as initial evidence of a favorable result. Overall response rate will be accompanied by an exact 95% confidence interval. To determine the role of iPS *in-vitro* response to Trikafta™, we will compare the  $\Delta$  Isc (change in Isc) among Trikafta™ responders and Trikafta™ non-responders using an ANCOVA test. Additionally, we will correlate the  $\Delta$  Isc obtained from *in vitro* experiments with the change in FEV1% predicted (post minus pre) using Spearman's rank-order correlation with an associated 95% confidence interval. We will also test whether the iPS response reaches a CFTR functional threshold of 30% wild-type levels (a magnitude of activity in primary airway epithelial cells viewed as potentially relevant to clinical benefit). In a sensitivity analysis, we will replicate the FEV1 analysis with sweat chloride responses and determine the *in vivo* response rate.

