**Protocol Title: Evaluating Trikafta for the treatment of patients with non-cystic fibrosis bronchiectasis (NCFBE)**

subject research, we will evaluate therapeutic response in individual subjects by an interrupted time series (ITS) method. Briefly, in the absence of an independent control group, ITS analysis is a quasi-experimental design in which each subject acts as their own control and is followed serially in time prior to and after an interruption (in this case, the start of treatment). If the treatment has causal impact, the post-intervention time series will have a different level or slope than the pre-intervention series. Time series models also have the power to test and correct for possible cyclical patterns and outliers. Using segmented regression analysis, we will conduct ITS models for each of the subjects enrolled in the trial. A significant change in slope from the pre-treatment period will indicate a significant treatment effect. ITS models will be constructed for each outcome of interest where historical and pre-treatment data are available. The change in slope will also be correlated with the *in-vitro* response using Spearman's rank-order correlation coefficient.

All analyses will be conducted using the intention to treat principal, where all subjects will be included in analysis regardless of how long they took the study medication. Statistical significance will be assessed at the 0.05 level and analyses conducted using SAS v. 9.4 (SAS Institute; Cary, NC).

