**Sample size**

We will test the null hypothesis that the true Trikafta™ response rate of NCFBE individuals is  $\leq 1\%$  vs. the alternative hypothesis that the true Trikafta™ response rate is  $\geq 15\%$ . We will initially enroll 16 subjects. If none of these subjects exhibit a clinical response (defined as  $> 5\%$  improvement of % predicted FEV1 from baseline), the study may be considered for termination. Otherwise, we intend to enroll a total sample size of 29 individuals (or 30 subjects, in the unlikely event that an individual discontinues participation; i.e., subjects who do not complete the study will be replaced). In this design, if Trikafta™ is ineffective, the probability of early termination after 16 subjects is 85% and only a 2.8% chance of concluding the drug is effective (type I error). If Trikafta™ is effective, there is a 90.04% chance of reaching this conclusion. If fewer than 2 patients (of 29 patients total) of the overall cohort show a clinical effect, Trikafta™ will be considered ineffective. To demonstrate the ability of iPS cells to predict clinical benefit, 16 (29) patients will provide at least 80% power to detect a significant Spearman correlation of at least  $r = 0.8$  (.53) between the changes in clinical outcomes with changes in short circuit current as measured in iPS cells. Tabular details of this analysis are provided below. Power calculations were performed using PASS v. 14 (Kaysville, UT) with a two-sided Z-test and a significance level of 0.05.

|                            | Cumulative # of responses | Decision                                                                                                             | 95% Confidence Interval (CI) |
|----------------------------|---------------------------|----------------------------------------------------------------------------------------------------------------------|------------------------------|
| Stage 1: Enter 16 subjects | 0                         | Consider Termination of the trial because the agent is ineffective.
Response rate is <math>\leq 1\%</math> | LB of 95% CI is $< 1\%$      |
|                            | At least 1                | Inconclusive result, continue                                                                                        | 95% CI contains 1%           |

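### The exclusion for changes in pulmonary therapy looks back only from screening, although the FEV1 baseline is Day 1, up to 28 days later

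*Protocol*

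**What the plan says.** Four parts of the protocol bear on this.

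- **Eligibility on therapy change** (Section 11, Exclusion Criteria): "Pulmonary exacerbation or changes in therapy for pulmonary disease in the 4 weeks prior to screening". The only reference date is screening.
- **Eligibility on stability** (Section 11, Inclusion Criteria): "Clinically stable in the past 4 weeks with no evidence of bronchiectasis exacerbation (prior to Screening AND Day 1". This has two reference dates, and it names clinical stability and exacerbation, not a change of therapy.
- **Related criteria** (Section 11): the last inclusion criterion is "Agreement to adhere to all current medical therapies as designated by the study physician". A discretionary exclusion covers "Any other condition that in the opinion of the lead investigators might confound results of the study".
- **Timing and analysis**: the schedule in Section 6 places screening anywhere from Day -28 to Day -1 and labels Day 1 as baseline. Section 7 says "A responder is defined as any subject with an improvement, from baseline, in" FEV1 of more than 5% predicted, assessed at week 4. The same section acknowledges that the interrupted time series analysis is used "in the absence of an independent control group", and it states that "all subjects will be included in analysis regardless of how long they took the study medication". Concomitant medication is recorded at every visit, but no consequence of a change is stated for eligibility or responder status.

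**The concern.** The protocol carries stability and exacerbation forward from screening to Day 1 but leaves therapy change behind. The exclusion criterion lists exacerbation and therapy change as alternatives, so the protocol itself treats them as different events; a subject can be stable and still have treatment altered. Elsewhere the same exclusion list extends its windows forward where that is intended, as for mycobacterial therapy and other investigational drugs. The therapy-change item has no such extension.

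What is at stake is attribution. With a before/after comparison and no control arm, FEV1 gained after Day 1 from a newly started background therapy cannot be told apart from gain due to the study drug. The decision rule in Section 7 (Sample size) sets the null response rate at 1%, and its lower positive category needs only two responders, so a small number of non-drug responders can move the result.

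**Working it through.** **Step 1: the gap in the text.** Take a subject screened on Day -28 whose pulmonary therapy is changed shortly before Day 1.

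- Therapy-change exclusion: not met, because it looks back from screening.
- Stability criterion: satisfied, provided the subject is clinically stable without an exacerbation.
- Adherence agreement: asks subjects to keep to therapies the study physician designates. It does not say that an added or altered therapy disqualifies.
- Discretionary exclusion: depends on investigator opinion and refers to a condition.
- Withdrawal for a newly developed exclusion criterion (Section 15): a change after screening never meets a criterion that looks back from screening.

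The subject stays eligible under every stated rule.

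**Step 2: reproduce the stated design.** Inputs from Section 7 (Sample size): "We will initially enroll 16 subjects", consider stopping at 0 responses, continue to 29 in total, and treat fewer than 2 of 29 as ineffective; null rate 1%, alternative 15%. With the stage 1 stop applied,

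P(at least 2 of 29) = 1 − (1−p)^16 − 16p(1−p)^28.

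- Early stopping at p = 0.01: 0.99^16 = 0.8515 (stated 85%).
- Type I error at p = 0.01: 1 − 0.8515 − 0.16 × 0.7547 = 0.0278 (stated 2.8%).
- Power at p = 0.15: 1 − 0.0743 − 2.4 × 0.01056 = 0.9004 (stated 90.04%).

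All three stated figures are reproduced.

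**Step 3: illustrate the effect with an inert drug.** Let f be the share of subjects whose pulmonary therapy changes between Screening and Day 1, and q the chance that this change alone adds more than 5% predicted after Day 1. Neither is in the documents; both are assumptions. The background response rate becomes p = 0.01 + 0.99·f·q, and the formula of Step 2 gives:

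| f | q | p | P(at least 2 of 29) |
|---|---|---|---|
| 0 | – | 0.0100 | 2.8% |
| 5% | 10% | 0.0150 | 5.7% |
| 5% | 20% | 0.0199 | 9.4% |
| 10% | 20% | 0.0298 | 17.9% |
| 10% | 30% | 0.0397 | 27.3% |

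**Step 4: condition on exactly one false responder, the other 28 at 1%.**

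- In stage 1: one more is needed among 28, so 1 − 0.99^28 = 24.5%.
- In stage 2: stage 1 must itself produce a responder among 16, so 1 − 0.99^16 = 14.9%.

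**The case against.** The strongest defence is that little is left uncovered. The subject must be clinically stable before Day 1, has agreed to adhere to current therapies, and can be excluded if the investigators see a confounding condition. A patient whose worsening prompted new treatment would be hard to call stable. This is fair: what remains is an elective change in a stable subject that no investigator judges confounding. It is narrow, but no stated criterion closes it.

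Second, spirometry is repeated on Day 1, so benefit reached by then is in the baseline. After screening, spirometry is normally done before bronchodilator, with withholding times, which blunts the effect of a new bronchodilator. Both points stand. A reader might infer that the whole benefit of a therapy started after screening would be credited to the drug; only the part gained after Day 1 would be, so changes made shortly before Day 1 matter most.

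Third, a reader might take 24.5% or 14.9% as the trial's true type I error. The documents do not support that: both figures presuppose that a false responder already exists. Nor do two responders amount to a declaration of efficacy. The decision table says only that the drug may be effective at 2 or more, and reserves the firm conclusion for 6 or more. Section 7 separately regards a rate of at least 15% as initial favourable evidence, which is 5 of 29 (0.15 × 29 = 4.35). With one false responder and 28 subjects at 1%, reaching 5 needs at least 4 of 28, a probability of about 0.0002. The sensitivity in Step 3 comes from pairing a 1% null with a cutoff of two, and any non-drug variation in FEV1 would exploit it.

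Finally, the absence of a sensitivity analysis for therapy changes is not a fault here. Such an analysis is commonly left to the statistical analysis plan, which is not at hand. A rule that denied responder status after any recorded change would also penalise therapy reduced because the patient improved.

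**Conclusion.** The two criteria are misaligned, and the misalignment leaves a real but narrow entry gap: a clinically stable subject with pulmonary therapy started or changed between Screening and Day 1 is not excluded. Any further FEV1 gain from that therapy after Day 1 would count toward drug response, with no control to separate the two.

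The size cannot be fixed from the documents, because they give neither the frequency of such changes nor their effect on FEV1. Over the assumed range from f = 5%, q = 10% to f = 10%, q = 30%, the chance that an inert drug reaches the lower positive category rises from the stated 2.8% to between about 6% and 27%. These figures are illustrative and treat the stage 1 stop as applied, as the protocol's own figures do. The textual point does not depend on them. The correction is worth making because it is cheap and eligibility is fixed in the protocol, so no later analysis plan can close the gap at entry.

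**What to change.** Reconcile the two criteria in Section 11 so that the therapy-change exclusion has the same reference dates as the stability criterion, namely Screening and Day 1. This takes a few words. The information needed is already collected, since concomitant medication is reviewed at Screening and Day 1. The cost is an occasional delayed Day 1 or re-screen.

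The edit addresses entry only. It does not reach therapy changes made between Day 1 and Day 28.

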**12. Population**

The following populations will be excluded from participation in this study:

- Adults unable to consent
- Individuals who are not yet adults (infants, children, teenagers)
- Pregnant women
- Prisoners
- Cognitively impaired or Individuals with Impaired Decision-Making Capacity
- Individuals who are not able to clearly understand English

There are no exclusions based on race or ethnicity. Further, we are not utilizing racial and ethnic classification of subjects for descriptive statistics, within an explanatory model, or as a variable to explain differences between patients.

**13. Local Number of Participants**

---

## **Protocol Title: Evaluating Trikafta for the treatment of patients with non-cystic fibrosis bronchiectasis (NCFBE)**

---

We anticipate that the 'lead-in' study (to gain information regarding numbers of individuals with NCFBE who may be eligible for the drug treatment ('main' trial) will primarily include patients at Emory followed with a diagnosis of bronchiectasis (who do not have clinical criteria sufficient for a diagnosis of cystic fibrosis). Approximately 300 participants will be accrued locally into the 'lead-in' study.

Subjects who exhibit a single CF-causing mutation in CFTR and/or sweat chloride 30-60 mEq/L will be approached about their interest in reviewing the consent form for the 'main' study (i.e., involving iPSC derivation and *in vivo* Trikafta™ treatment for 4 weeks). We will enroll 30 subjects accrued locally or via physician referral.

For the 'main' study, we plan to recruit 30 subjects with NCFBE. We intend to include ~50% female and ~50% male subjects age ≥ 18. Subjects will be referred from clinicians participating in the trial (Emory University, Atlanta), or from outside institutions. We anticipate that the study population will be 50% male, but >80% white, since most individuals who are carriers of a CFTR mutation are Caucasian. However, efforts will be made to enroll study subjects from non-Caucasian populations who are eligible (e.g., by conducting full exome CFTR analysis to identify rare CFTR mutations found more frequently among non-white individuals, and utilizing mildly elevated sweat chloride as an entry criterion (i.e., in addition to genotype)). Findings from the 'lead-in' study will be compiled in anonymous fashion and using patient identification numbers as described in Section 8. Because CFTR genotypes and sweat chloride for the 'lead-in' study will typically be conducted in a non-CLIA research laboratory, this screening data will not be included in the patient medical record. For subjects who enroll in the 'main' study, report of genotype and CLIA approved sweat testing will be performed and results entered in the medical record.

### **14. Recruitment Methods**

In order to gain information regarding numbers of individuals with NCFBE who may be eligible for our trial, patients at Emory followed with a diagnosis of bronchiectasis (who do not have clinical criteria sufficient for a diagnosis of cystic fibrosis) will be asked to consider participating in a 'lead in' study that will determine the subject's CFTR genotype and sweat chloride. A separate consent form will be utilized for the 'lead in' study. Subjects who exhibit a single CF-causing mutation in CFTR and/or sweat chloride 30-60 mEq/L will be approached about their interest in reviewing the consent form for the 'main' study ("iPSC derivation and *in vivo* Trikafta™ treatment for 4 weeks")

We have currently identified 7-8 potential subjects for the 'main' study based on known clinical findings among these individuals. Data from the 'lead-in' study (CFTR mutation analysis – predeominantly for the common F508del variant and sweat chloride level) will typically be conducted in a research laboratory (non-CLIA approved), and will not be included in the patient record.

**Protocol Title: Evaluating Trikafta for the treatment of patients with non-cystic fibrosis bronchiectasis (NCFBE)**

---

Subjects will be referred from clinicians participating in the trial (Emory University, Atlanta), or from outside institutions. We estimate up to 30% of subjects may be referred from outside institutions, primarily involving individuals from the Atlanta area.

## **15. Withdrawal of Participants**

Criteria for discontinuing the 'main' study intervention (e.g., halting rules), may include any monitoring test(s) and associated clinical decision point(s) which in the opinion of the clinical investigators, qualified designees, or Data Monitoring Committee are viewed as placing the patient at significant risk if Trikafta™ administration is to continue. This could include, for example (but is not limited to) worsening liver function or abnormalities associated with Trikafta™ administration (see also below). Discontinuation from Trikafta™ does not mean discontinuation from the 'main' study, and remaining study procedures should be completed as indicated by the study protocol and lead investigators. If a clinically significant finding is identified (including, but not limited to changes from baseline) after enrollment, the investigators or qualified designees, and/or Data Monitoring Committee (also referred to as Data Safety Monitoring Committee, DSMC) will determine whether any change in participant management is needed. Any new clinically relevant adverse finding will be reported as an adverse event (AE).

The data to be collected at the time of 'main' study intervention discontinuation will include:

- All measurements described for the day 56 follow-up/washout visit

Participants are free to withdraw from participation at any time upon request.

An investigator may discontinue or withdraw a participant from the study for the following reasons:

- If any clinical adverse event, laboratory abnormality, or other medical condition or situation occurs such that continued participation in the study would not be in the best interest of the participant
- Disease progression which requires discontinuation of the 'main' study intervention
- If the participant meets an exclusion criterion (either newly developed or not previously recognized) that precludes further study participation
- Participant is unable to receive Trikafta™ for 3 days
- Pregnancy
- Significant study intervention non-compliance

The reason for participant discontinuation or withdrawal from the 'main' study will be recorded. An attempt will be made to replace subjects who sign the informed consent form and receive Trikafta™, and subsequently withdraw, or are withdrawn or discontinued from the study.

